### Statistical Analysis

Data entry, consistency check, and cleaning will be performed prior to analysis. Mean and standard deviation will be used for continuous variables, while frequency and percentages will be used to describe categorical variables. We do not anticipate this study will detect statistically significant findings however, as part of a secondary analysis, unpaired *t* tests will be used. Differences between intervention and control groups with respect to outcomes will be compared using repeated measures ANOVA or independent *t* test split by group. Data analysis will be conducted using SPSS statistical software. A *P*<0.05 will be used to determine potential significance. The 95% CI for differences will also be calculated. With respect to dropout, every person who is randomized regardless or subsequent fall, death, or admission to LTC will be included in the final analysis. If participants drop out before the intervention or voluntarily withdraw they will not be included in the final analysis. For analysis of the clinical assessments tracked over the course of the study (schedule of assessment described in Table 1), intention-to-treat analysis will be used by carrying the last observation forward.

Qualitative analysis will follow the Framework Method [47]. This method helps build rigor and trustworthiness in qualitative analysis by providing a clear audit trail from the original data to the final themes including illustrative quotations.

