### Study Design

#### Overview

The study was approved by the local research ethics authority. This is a cluster randomized feasibility trial assessing 4 rural regions (2 per study arm) comparing usual rural community-based dementia care to Telegerontology plus usual rural community-based dementia care. Using the opaque envelope method, the rural regions will be randomized to control or intervention after baseline assessment. The intervention will last 6 months with the measurement of outcomes taking place at baseline, after 6 months (post), with follow-up occurring 6 months (6-month follow-up) and 12 months (12-month follow-up) after cessation of the intervention.

The study population will include 22 “dementia triads” that consist of a community-dwelling older Canadian with moderate to late dementia, their family caregivers, and their PCP. The study will be carried out in communities located in rural areas of Newfoundland and Labrador, Canada but will be monitored remotely from the metropolitan city of St John’s, Newfoundland and Labrador. We define *rural* in this study to mean a community with less than 10,000 residents and a location that is greater than two hours’ drive from the metropolitan city, where specialist health services are located. Before randomization, recruitment will begin by enrolling PCPs from rural communities who will make initial contact with potential participants. Written informed consent will be obtained for every individual agreeing to participate in the study except in the case for an individual with advanced dementia who lacks capacity, in which case consent will be obtained from the substitute decision maker. Consent will be reviewed without the presence of the PCP in order to limit undue influence for participation in the study.

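### Regions are randomised (two per arm), but the stated t tests and repeated measures ANOVA have no region term, so P values and 95% CIs are too optimistic if outcomes correlate within region

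*Protocol article*

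**What the plan says.** The Overview under Study Design fixes the unit of allocation: "This is a cluster randomized feasibility trial assessing 4 rural regions (2 per study arm"). It adds that "the rural regions will be randomized to control or intervention after baseline assessment". The Abstract and the legend of Figure 1 agree that regions are allocated.

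The Statistical Analysis section then names the methods: "Differences between intervention and control groups with respect to outcomes will be compared using repeated measures ANOVA or independent" *t* tests split by group. It sets a decision rule, P<"0.05 will be used to determine potential significance", and states that "The 95% CI for differences will also be calculated". No region term, region-level summary, design effect or ICC appears there or elsewhere in the article. The rule on who is analysed refers to "every person who is randomized", although no person is randomised in this design.

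The same section also limits its claims: "We do not anticipate this study will detect statistically significant findings however, as part of a secondary analysis, unpaired" *t* tests will be used. The Sample Size Calculation section says the number was set from regional population figures and not for power. Study Strengths and Limitations mentions small sample size and variability between participants, but neither clustering nor the small number of regions.

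**The concern.** An independent t test treats every person as a separate random allocation. Repeated measures ANOVA allows for correlation between visits of the same person, but not for correlation between different people in the same region. With two regions per arm, any real difference between regions goes straight into the arm difference, and neither method counts it as error.

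Correlation within region is plausible for emergency room visits, hospital stays and admission to long-term care, which depend on local services, and the primary care physicians (PCPs) who refer patients also manage their treatment changes. This is an inference: the article does not say how many physicians, hospitals or long-term care facilities each region has.

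At stake is the reading of the arm comparison. The first objective is to test whether Telegerontology improves care in place, and the Outcome Measures section says the outcomes will answer that primary research question. The trial is also meant to inform a full-scale RCT. Intervals that are too narrow would overstate what four regions can show.

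**Working it through.** **Inputs from the article.** Four regions, two per arm (Overview). Study population: "The study population will include 22" triads (Overview). Recruitment target: 42 participants (Sample Size Calculation). Alpha 0.05, taken as two-sided because sidedness is not stated. Both 22 and 42 are carried through, because both appear in the article.

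**The plan's own figure.** 38,490 × 98.5/1000 × 0.34 = 1,289 community-dwelling patients; × 2.5% = 32.2; × 1.3 for dropout = 41.9, that is 42. The figure reproduces, and it contains no allowance for clustering.

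**Assumptions.** The ICC is not given, so 0 to 0.10 is assumed. Regions are taken as near equal: 22/4 = 5.5 or 42/4 = 10.5 people each. Outcomes in the simulation are normal, which simplifies the counts and the admission date.

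**Design effect**, 1 + (m − 1) × ICC:
- m = 5.5: 1 + 4.5 × 0.05 = 1.225; 1 + 4.5 × 0.10 = 1.45. Effective size at ICC 0.10: 22/1.45 = 15.2.
- m = 10.5: 1 + 9.5 × 0.05 = 1.475; 1 + 9.5 × 0.10 = 1.95. Effective size at ICC 0.10: 42/1.95 = 21.5.

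**True type I error of the nominal 5% person-level t test** (100,000 simulated null trials per setting, two regions per arm):

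| Assumed ICC | 22 people | 42 people |
|---|---|---|
| 0 | 5.0% | 5.0% |
| 0.01 | 5.5% | 6.1% |
| 0.02 | 6.0% | 7.1% |
| 0.05 | 7.7% | 10.7% |
| 0.10 | 10.7% | 16.8% |

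Coverage of the nominal 95% CI is one minus these values: at ICC 0.10, about 89% with 22 people and 83% with 42. A t test on the four region means stays at about 5% in every setting.

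**Degrees of freedom.** Four region means less two arm means leave 2 df. The critical t is 4.30, against 2.09 on 22 − 2 = 20 df and 2.02 on 42 − 2 = 40 df.

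**Interval width.** In simulation, the region-level 95% CI is on average about 1.9 times as wide as the person-level one at ICC 0, and about 2.3 times (22 people) or 2.7 times (42 people) at ICC 0.10. The ratio of critical values, 4.303/2.086 = 2.06, is not a lower bound, because a standard error estimated on 2 df is often small by chance. With 22 people at ICC 0, the region-level interval is the narrower of the two in about 19% of trials.

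**Randomisation test.** Choosing 2 of 4 regions gives 6 allocations. The smallest possible two-sided P is 2/6 = 0.33, so such a test can never reach P<0.05.

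**The case against.** The strongest reply is that this is a feasibility trial. The article calls the t tests secondary, expects no significant findings, did not size the study for power, and attaches no progression rule to P<0.05. That stands, and it lowers the severity. It does not remove the point, because the P<0.05 rule and the 95% CIs remain in the text and the first objective is still a test of the intervention.

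A second reply is that the ICC may be close to zero. This also stands in part: at 0.01-0.02 the inflation is modest, and at zero the person-level test and interval are valid. But four regions cannot show that the ICC is negligible.

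A third is that an article leaves modelling detail to an analysis plan. That would excuse silence. Here the article names specific tests that do not match its own unit of randomisation.

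Three stronger readings are tempting but unsupported. A reader might infer that the P values are certainly too small; that needs a positive ICC, which the article does not give. A reader might take it as fact that people in a region share an emergency room, a hospital and long-term care beds; the article does not describe local services. And a reader might conclude that a valid interval must be at least twice as wide even without clustering; at ICC 0 the person-level interval is already valid, and the average ratio is about 1.9.

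**Conclusion.** The stated analysis does not match the stated design: allocation is by region, and the comparison takes no account of region. This is wrong as written and does not depend on a missing analysis plan.

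The size does depend on an assumption. Over ICC 0.01 to 0.10, true type I error runs from about 5.5% to 11% with 22 people and from about 6% to 17% with 42, assuming normal outcomes and near-equal regions. The person-level reading of the test is itself drawn from the named methods, the absence of any region term and the reference to randomised persons; the article does not use the term.

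The severity is should-fix: the tests are secondary and openly underpowered, but the intervals may be read as evidence for the full-scale trial.

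**What to change.** In the Statistical Analysis section:

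- Delete the P<0.05 rule for potential significance.
- Report each outcome descriptively by arm and for each of the four regions.
- Base any arm difference and its 95% CI on the four region summaries, with 2 df.
- Reword the rule on who is analysed so that it refers to people in randomised regions.

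Do not offer a mixed model with a random region effect as equivalent. With four regions, a moment estimate of the region variance is zero or negative in about 45% (22 people) or 36% (42 people) of simulated trials even at ICC 0.10, and the region effect then drops out. If an ICC is reported for planning, say that four regions make it very imprecise.

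The cost is a few sentences and simple code, with no new data. The downside is wider intervals and almost no power for the arm comparison, which is what two regions per arm can support.

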#### Primary Outcomes

Primary outcomes will be reported by caregivers and confirmed through medical records and chart reviews (schedule of assessment described in Table 1). Based on Canadian incidence rates, we anticipate these outcomes will be detectable during the 18-month study period [33-35]. The primary outcomes will be as follows:

Admission to long-term care (LTC): Date that participant is admitted to LTC.Emergency room (ER) visits: Total number of ER visits over 6 months.Falls: Total number of falls over 6 months.Hospital stays: Total number of hospital stays over 6 months.Caregiving Hassles Scale: This 42-item scale assesses the daily burden of caring for a family member with dementia. Caregivers are asked to rate patient requirements and behaviors on a 5-point scale of frequency, ranging from “Did not occur” to “A lot.” High scores indicate higher level of caregiver burden. Assessment takes 20 minutes to complete [28]. Administered by iPad, at pre, post, 6- and 12-month measures, in addition to an outcome measure, this scale will be used as a monitoring tool during the intervention at the discretion of the Telegeronology physician.

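### Caregiving Hassles Scale: two non-equivalent tests are left open, no visit or ANOVA term is named, and neither test uses the baseline score as a covariate

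*Protocol article*

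**What the plan says.** All references are to the protocol article.

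- **Test.** Statistical Analysis: "Differences between intervention and control groups with respect to outcomes will be compared using repeated measures ANOVA or independent" *t* "test split by group". The sentence covers outcomes in general. It does not say which outcome or visit gets which test, or which ANOVA term is the arm comparison.
- **Status.** The same section says "We do not anticipate this study will detect statistically significant findings however, as part of a secondary analysis, unpaired" *t* tests will be run. It sets a *P* value "<0.05 will be used to determine potential significance" and adds that "The 95% CI for differences will also be calculated".
- **Schedule.** Primary Outcomes has the Hassles Scale measured "at pre, post, 6- and 12-month measures", and Table 1 agrees. Regions are randomised after the baseline assessment (Study Design, Overview), so the baseline score precedes randomisation.
- **Who is analysed.** Statistical Analysis: "every person who is randomized regardless or subsequent fall, death, or admission to LTC will be included in the final analysis". Voluntary withdrawals and people lost before the intervention are left out. LOCF is stated for the clinical assessments tracked through the study.
- **Where Hassles sits.** Table 1 lists it under Outcome Measures, not under Clinical Assessment Tools. The text also lists it under Remote Assessment Tools, beside the agitation and depression scales, which Table 1 does place under Clinical Assessment Tools.

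**The concern.** The two named tests do not estimate the same quantity. The independent *t* test compares one follow-up visit and takes no account of where each dyad started. The repeated measures ANOVA offers two candidate terms with different meanings. A plan that fixes neither the test nor the term leaves the choice open until the data are seen.

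The article says the trial should inform a full-scale trial, so an arm difference and its interval are what carry forward. Study Strengths and Limitations itself expects considerable variability between participants. Adjusting for a score already collected before randomisation would reduce that variability, and neither option does this.

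There is also a question of fit. Classical repeated measures ANOVA needs a score at every visit, whereas the inclusion rule keeps people who die or enter long-term care.

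**Working it through.** **Inputs.** From the document: four Hassles visits (one before randomisation, three after), significance level 0.05, four regions with two per arm, 22 triads (Abstract and Study Design) and a recruitment target of 42 (Sample Size Calculation). The 42 reproduces: 38,490 × 0.0985 × 0.34 = 1,289; × 2.5% = 32.2; × 1.3 = 41.9. The document gives no power, effect size, SD or correlation for this outcome. Assumed here: SD 1, the same correlation r between any two visits, r = 0.5 to 0.7, a constant effect d at all three follow-ups, independent patients and two-sided tests.

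**1. What each option estimates.** Variances are relative to the unadjusted post *t* test, set at 1.

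| Analysis | Expected contrast | Variance | r = 0.5 | r = 0.7 |
|---|---|---|---|---|
| *t* test at post | d | 1 | 1 | 1 |
| Baseline-adjusted score at post | d | 1 − r² | 0.75 | 0.51 |
| ANOVA group main effect, 4 visits | (0+d+d+d)/4 = 0.75d | (1+3r)/4 | 0.625 | 0.775 |
| Mean follow-up minus baseline | d | (1+2r)/3 + 1 − 2r | 0.667 | 0.400 |
| Baseline-adjusted mean follow-up | d | (1+2r)/3 − r² | 0.417 | 0.310 |

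**2. Like-for-like gains.**
- At post, adjusted against unadjusted: variance falls to 0.75 (r = 0.5) or 0.51 (r = 0.7).
- Mean follow-up, adjusted against change from baseline: 0.667/0.417 = 1.6 and 0.400/0.310 = 1.3.
- Adjusted post score against the ANOVA main effect, rescaled by 0.75² = 0.5625: 0.625/0.5625 = 1.11 and 0.775/0.5625 = 1.38. The ratios are 1.11/0.75 = 1.5 and 1.38/0.51 = 2.7. They apply only if the main effect is the term read.

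**3. Group-by-time term.** This is not diluted. With four visits and two arms it is a 3-degree-of-freedom test of any difference in profile, so by itself it does not give an arm difference with a 95% CI.

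**4. Simulated power at an assumed d = 0.8** (4,000 runs per cell):

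| Test | N=22, r=0.5 | N=22, r=0.7 | N=42, r=0.5 | N=42, r=0.7 |
|---|---|---|---|---|
| *t* test at post | 44% | 43% | 72% | 72% |
| ANOVA group main effect | 40% | 32% | 67% | 58% |
| ANOVA group-by-time | 44% | 68% | 75% | 94% |
| Baseline-adjusted score at post | 52% | 69% | 83% | 94% |

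The main effect is not always the weaker choice. At r = 0.3 and N = 22, the normal approximation gives it 53% against 47% for the *t* test.

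**5. Type I error when the choice is made after seeing the data** (N = 22, 32 and 42; r = 0.5 and 0.7; nominal 5%):
- post *t* test or group main effect: about 7-8%;
- also the group-by-time term: about 11-13%;
- also *t* tests at the 6- and 12-month follow-ups: about 15-17%.

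**6. Incomplete cases.** A dyad missing any visit is dropped from a classical repeated measures ANOVA. If LOCF covers Hassles, most of this disappears. If it does not, people who die or enter long-term care before the last visit are lost from that analysis despite the inclusion rule. The Outcome Measures placement in Table 1 points one way and the Remote Assessment Tools listing points the other.

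**The case against.** The tests are secondary, significance is not expected, intervals are promised, and the sample was not sized for power. A condensed article commonly leaves model terms and covariates to an analysis plan. The word *or* may simply assign tests by outcome, since Table 1 shows no baseline value for the event counts. All of this lowers the stakes. It does not remove the point, because the article does fix a pair of tests and a *P* threshold, and neither test is baseline-adjusted.

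Several stronger readings are tempting but not supported:

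- **That no usable arm comparison exists.** The group-by-time term is one, and at r = 0.7 its power nearly equals that of the baseline-adjusted test.
- **That "test split by group" means analysing each arm separately in SPSS.** The sentence opens with differences between the groups, and the preceding one says the *t* tests are unpaired. An arm comparison is plainly intended, and the phrase is only loose.
- **That the plan both ignores baseline and dilutes the effect.** The first applies to the *t* test and the second to the ANOVA main effect. No single test has both faults, and the article never says the main effect will be read.
- **That adjustment is 2.7 to 4.4 times as efficient.** Those ratios set the adjusted mean of three follow-ups against the diluted main effect. For the post contrast recommended here they are 1.5 to 2.7.
- **That the ANOVA would cost 30% of the sample.** The 30% is planned dropout, which the Dropout section defines as withdrawal or failed contact, not death or long-term care. The plan itself excludes voluntary withdrawals.

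**Conclusion.** The point holds for the Hassles Scale, as an improvement that is nearly free rather than a flaw that invalidates the trial. The article leaves two non-equivalent tests open, names no visit or term, and does not use a pre-randomisation score as a covariate. Leaving the choice open can raise type I error to about 7-8% with two options and to 15-17% with five. Adjustment at post reduces variance to 0.75-0.51 of the unadjusted *t* test. Against a change-from-baseline contrast the gain is smaller, about 1.6 to 1.3 times.

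These sizes rest on an assumed correlation of 0.5-0.7, equal correlation between visits and independent patients; the power figures also assume an effect of 0.8 SD. With two regions per arm, actual precision would be lower for every method. The conflict with the inclusion rule is conditional: it arises only if LOCF does not cover this scale, and the text is unclear on that.

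**What to change.** For the Hassles Scale, replace the sentence with one analysis: a mixed model of the post, 6-month and 12-month scores with baseline score as covariate and terms for arm, visit and arm-by-visit, using all available observations and accounting for region. With only four regions, comparing region means of baseline-adjusted residuals is an acceptable alternative. Name the arm difference at post, with its 95% CI, as the reported contrast, and delete the *t* test alternative for this outcome.

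Also state whether LOCF applies to Hassles and how dyads with no post-baseline score are handled. The mixed model does not settle the latter: with baseline only as a covariate, such a dyad contributes nothing, so the inclusion rule needs its own sentence.

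The cost is wording and slightly more analysis work. The baseline and follow-up scores are already in the schedule, and the Results section reports data collection as complete.

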##### Dropout

Dropout is defined as any participant who voluntarily withdraws or who cannot be successfully contacted within a month of the defined follow-up times. The impact of dropouts on statistical analysis, including intention to treat, will be discussed subsequently.

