### Sample Size Calculation

Sample size was calculated based on regional population statistics rather than for statistical power, targeting 2.5% of the population of community-dwelling dementia patients in the target region. Based on prevalence estimates, 98.5/1000 Canadians over 40 years of age have dementia with 34% living at home. The total population for the entire recruitment region of the present study is approximately 38,490 suggesting that the total population of community-dwelling dementia patents is approximately 1,289. Therefore, we aim to recruit 42 participants for inclusion in this study accounting for a 30% dropout rate.

**Table 2 table2:** Occupational Therapy Home Safety Video checklist.

Video	Description
1	A short video walking from the driveway outside, going into the house through the usual entry door, straight through the kitchen/living area into the person's bedroom and then into the bathroom.
2	Kitchen (short video)
3	Bedroom (short video)
4	Bathroom (short video)
5	Living room (short video)
6	Stairs (short video)
7	Laundry (short video)

Qualitative interview questions.PCP Interview QuestionsDescribe the care required to manage people with dementia in their homes.From your point of view, how well are your patients being managed at home?How would you envision an ideal circle of care to maintain people with dementia in their homes?Caregivers Interview QuestionsFrom your point of view, how well are you managing the health of your loved one at home?In an ideal world, how could things be improved? What are the main challenges you experience? Have you had successes caring for your loved one?

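### The plan removes voluntary withdrawers from the final analysis even after their region has been randomised, against its own all-randomised rule and its intention-to-treat rule for the tracked assessments

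*Protocol article*

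**What the plan says.** All of this is in the protocol article.

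- Statistical Analysis, on who is kept: "every person who is randomized regardless or subsequent fall, death, or admission to LTC will be included in the final analysis".
- Statistical Analysis, the next sentence, on who is removed: "If participants drop out before the intervention or voluntarily withdraw they will not be included in the final analysis".
- Statistical Analysis, on the clinical assessments tracked over time: "intention-to-treat analysis will be used by carrying the last observation forward".
- Dropout: "Dropout is defined as any participant who voluntarily withdraws or who cannot be successfully contacted within a month of the defined follow-up times". The same section adds: "The impact of dropouts on statistical analysis, including intention to treat, will be discussed subsequently".
- Study Design, Overview, on timing: "the rural regions will be randomized to control or intervention after baseline assessment". The Figure 1 caption gives the same order, with physician recruitment, referral and home assessment first and randomisation of regions afterwards.
- Sample Size Calculation: "we aim to recruit 42 participants for inclusion in this study accounting for a 30% dropout rate".

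No other section restores withdrawn participants to the analysis of long-term care (LTC) admission, emergency room (ER) visits, falls, hospital stays or caregiver burden.

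**The concern.** Whether someone stays in the analysis should not depend on a choice made after allocation. Here it does. One arm has weekly video calls with a specialist physician and the other has usual care, and participants can see which they have. A strained caregiver might leave because the calls are an extra task, or because usual care plus an iPad offers little. Caregiver burden and health-care use are plausible reasons for leaving, and they are also what the primary outcomes measure. If leaving is related to both arm and outcome, the people left in the two arms are no longer comparable, and data already collected on the leavers are thrown away.

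There is also a practical problem. The paragraph tells the analyst to exclude a withdrawer from the final analysis and, for the tracked assessments, to carry that person's last value forward under intention to treat. Two analysts could build different datasets from it in good faith.

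**Working it through.** **Step 1. Set the rules side by side.**

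| Situation | Rule stated | Region already randomised? |
|---|---|---|
| Fall, death or LTC admission | Kept | Yes |
| Leaves after enrolment, before the region is randomised | Excluded | No |
| Leaves after the region is randomised, before the intervention starts | Excluded | Yes |
| Withdraws voluntarily during the 6-month intervention or the 12 months after it | Excluded; for tracked assessments, last value also carried forward | Yes |
| Cannot be contacted within a month of a follow-up time | No exclusion stated | Yes |

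The second row is harmless, because a person who leaves before allocation cannot have left because of it. The third and fourth rows are the fault. In the fourth, the two rules cannot both apply to the tracked assessments.

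**Step 2. How many could be removed.** Inputs from Sample Size Calculation: regional population 38,490; prevalence 98.5 per 1,000; 34% living at home; 2.5% targeted; 30% dropout.

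- Community-dwelling patients: 38,490 × 0.0985 × 0.34 = 1,289.0 (stated: about 1,289).
- Target: 1,289.0 × 0.025 = 32.2.
- With dropout: 32.2 × 1.30 = 41.9, rounded to 42. The stated figure is reproduced.
- Dropouts if 30% of the 42 leave: 0.30 × 42 = 12.6, so 12 to 13, leaving 42 × 0.70 = 29.4.

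This is a ceiling at the planned rate. It treats every dropout as a voluntary withdrawal or a pre-intervention loss. The Dropout definition also covers lost contacts, whom the exclusion sentence does not name.

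**Step 3. What exclusion could do to an estimate.** The document gives no withdrawal pattern, so this is an illustration on assumed values. Let the true LTC risk be p = 0.30 in both arms. Let a share d of one arm withdraw before any admission and be excluded, with nobody withdrawing in the other arm. Let LTC-bound participants withdraw r times as often as the rest.

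- Withdrawal among the rest: o = d / (p·r + 1 − p).
- Withdrawal among the LTC-bound: l = r·o.
- Risk seen in those analysed: p(1 − l) / (1 − d).

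For d = 0.30 and r = 2: o = 0.30 / 1.30 = 0.231, l = 0.462, observed risk = 0.30 × 0.538 / 0.70 = 0.231.

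| d | r = 1 | r = 2 | r = 3 |
|---|---|---|---|
| 0.10 | 30.0% | 28.2% | 27.1% |
| 0.20 | 30.0% | 26.0% | 23.4% |
| 0.30 | 30.0% | 23.1% | 18.8% |

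Against 30% in the other arm, the false difference is 0 when r = 1 and about 2 to 11 percentage points when r is 2 or 3. It favours whichever arm loses the people.

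**The case against.** The strongest defence reads the two sentences as a rule with an exception: falls, deaths and LTC admissions do not count as dropout, but withdrawal does. Read that way the wording is coherent. The resulting set is still not everyone randomised, and the exception still collides with last observation carried forward.

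The second defence is the type of trial. It has four regions, a sample not sized for power, no expectation of significant findings, and *t* tests described as secondary. That stands and lowers the severity. It does not remove the point, because the first objective is comparative, a P<0.05 threshold and 95% confidence intervals are planned, and the results are to inform a full-scale trial.

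Several stronger readings are tempting but unsupported:

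- A reader might infer that everyone excluded before the intervention was already allocated. Enrolment and the home assessment precede randomisation, so some may not have been.
- A reader might call the result a completer set. Deaths and LTC admissions are kept, and lost contacts are not excluded.
- A reader might infer that the pre-intervention exclusion acts differently by arm. Control and Intervention Group gives both arms a common 6-month active period, so the phrase may mean the same point for both.
- A reader might infer that no primary outcome has an intention-to-treat rule. The Caregiving Hassles Scale is a primary outcome but is also listed among the remote assessment tools and followed at every time point, so the carry-forward sentence may cover it.
- A reader might apply 30% to the 22 triads named in the Overview. The document attaches the 30% only to the 42.

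**Conclusion.** The point holds as a fault in a stated rule, not as an omission that an analysis plan might fill. What is certain is that allocated participants who withdraw are removed, that this departs from including every randomised person, and that it cannot be squared with the carry-forward rule in the same paragraph.

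Bias is a credible risk of unknown size. It needs withdrawal to be related to outcome, and related differently in the two arms; the documents contain no evidence on this either way. The range of 0 to about 11 percentage points rests wholly on the assumed LTC risk, one-sided withdrawal and withdrawal ratios above. A reader might take it as a forecast, and it is not one. At the planned dropout rate the number removed is at most about 12 to 13 of 42.

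This should be fixed before analysis. It does not invalidate a feasibility trial.

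**What to change.** Replace the exclusion sentence with a rule to this effect:

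- Exclude only people who leave before their region is randomised.
- Analyse everyone else, including lost contacts, by their region's allocation, using all data observed up to withdrawal or last contact as far as consent allows.
- Show the set without withdrawers as a sensitivity analysis, with the number withdrawn in each arm.

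The carry-forward sentence then applies to a defined set, and the two rules no longer clash.

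The main cost is that withdrawers contribute unequal observation time. ER visits, falls and hospital stays are defined as totals over 6 months, so a shortened period cannot enter as if it were complete. The analysis must allow for time observed, which goes beyond the planned *t* tests and repeated measures ANOVA. Data up to withdrawal also cannot show what happened later, so the change reduces selection without guaranteeing its removal.

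Primary Outcomes states: "Primary outcomes will be reported by caregivers and confirmed through medical records and chart reviews". Where consent allows, that review may supply LTC, ER and hospital data after withdrawal. It is not stated for referrals or physician visits, which are secondary. The Results section says data collection ended in April 2017, so further review may not be possible. The core fix does not depend on it and uses data already held.
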